## Abstract

**Background:**

Healthcare reform in the United States is encouraging Federally Qualified Health Centers and other primary-care practices to integrate treatment for addiction and other behavioral health conditions into their practices. The potential of mobile health technologies to manage addiction and comorbidities such as HIV in these settings is substantial but largely untested. This paper describes a protocol to evaluate the implementation of an E-Health integrated communication technology delivered via mobile phones, called Seva, into primary-care settings. Seva is an evidence-based system of addiction treatment and recovery support for patients and real-time caseload monitoring for clinicians.

**Methods/Design:**

Our implementation strategy uses three models of organizational change: the Program Planning Model to promote acceptance and sustainability, the NIATx quality improvement model to create a welcoming environment for change, and Rogers’s diffusion of innovations research, which facilitates adaptations of innovations to maximize their adoption potential. We will implement Seva and conduct an intensive, mixed-methods assessment at three diverse Federally Qualified Healthcare Centers in the United States. Our non-concurrent multiple-baseline design includes three periods — pretest (ending in four months of implementation preparation), active Seva implementation, and maintenance — with implementation staggered at six-month intervals across sites. The first site will serve as a pilot clinic. We will track the timing of intervention elements and assess study outcomes within each dimension of the Reach, Effectiveness, Adoption, Implementation, and Maintenance framework, including effects on clinicians, patients, and practices. Our mixed-methods approach will include quantitative (*e.g*., interrupted time-series analysis of treatment attendance, with clinics as the unit of analysis) and qualitative (*e.g*., staff interviews regarding adaptations to implementation protocol) methods, and assessment of implementation costs.

**Discussion:**

If implementation is successful, the field will have a proven technology that helps Federally Qualified Health Centers and affiliated organizations provide addiction treatment and recovery support, as well as a proven strategy for implementing the technology. Seva also has the potential to improve core elements of addiction treatment, such as referral and treatment processes. A mobile technology for addiction treatment and accompanying implementation model could provide a cost-effective means to improve the lives of patients with drug and alcohol problems.

**Trial registration:**

ClinicalTrials.gov (NCT01963234).

## Background

### Context

This paper describes the protocol for a study on implementing mobile-health technology in primary care. The study is funded by the United States’ National Institute on Drug Abuse as part of a request for proposals aimed at integrating addiction treatment into primary care*.* Although numerous smartphone applications exist that address many health problems, primary care clinicians do not commonly incorporate mobile technology into patient care
[1]. One reason is that very few smartphone applications have been proven in rigorous trials of effectiveness. Even if an application does have a reliable evidence base, it must still demonstrate its value to various stakeholders if it is to be widely used. Patients must see value in the application or they are likely to stop using it. Clinicians must find it useful to incorporate it in day-to-day clinical management. Finally, clinic administrators must find that the application works both clinically and financially to support its use by patients and staff.

Our study focuses on Federally Qualified Health Centers (FQHCs) in the United States, community-based organizations that provide primary care and preventive health services to patients regardless of their ability to pay. FQHCs (and U.S. primary-care practices in general) are increasingly being encouraged by healthcare reform to integrate treatment for addiction and behavioral health into their practices. HIV testing and prevention efforts are particularly important for the health of men and women who use illicit drugs because they are at higher risk than the general population for acquiring HIV
[2,3]. But transforming primary care to address addiction and HIV will likely add to the work of clinicians, many of whom already feel overburdened. Previous attempts to integrate addiction treatment into primary care have largely relied on labor-intensive solutions (*e.g*., adding more staff or having staff do tasks differently), with mixed results
[4].

Our premise is that mobile health technology holds great promise for FQHCs to reach this complex patient population. More than two-thirds of individuals with substance use disorders (SUDs) have had contact with a primary-care provider in the previous six months
[5], for reasons that may or may not relate to their SUD
[6]. But primary-care providers frequently do not screen for or treat SUDs, even though recovery support can be effectively administered in primary care
[6,7]. Administering recovery support requires that clinicians receive support and training in addiction, which are uncommon partly because of the traditional separation of addiction treatment from primary care
[8-10]. Technology may help address these problems. People with addictions tend to view technology favorably
[11]. They acknowledge more drug use and psychiatric symptoms online than in face-to-face interviews
[12]. A recent review found positive outcomes in 29 of 32 randomized trials using personal computers and cell phones for managing chronic diseases
[13]. While some information technologies have proven efficacious, penetration into practice has been slow
[14]. The potential of mobile health technologies to manage chronic diseases in FQHCs is substantial, but remains largely untested.

### The mobile-health technology

The integrated system we have developed is an E-Health integrated communication technology for patients with addiction called Seva (say’-va; a Sanskrit word for selfless caring). Seva consists of treatment and recovery support elements. The treatment component is based on the Therapeutic Education System (TES), a web- and mobile-based curriculum for addiction treatment with 65 interactive, multimedia, skill-building modules, including basic cognitive behavioral recovery support skills (*e.g*., refusing drugs, managing thoughts about drug use), life re-structuring skills (*e.g*., increasing recreational activities), and skills for preventing HIV, hepatitis, and sexually transmitted infections. Each module ends with a quiz structured to ensure mastery of key content and skills. TES uses interactive videos to create experiential learning environments that help patients learn modeled behaviors (*e.g*., progressive muscle relaxation). Randomized trials have found that TES is as efficacious as behavioral therapy delivered by therapists and is superior to standard substance abuse treatment
[15]; that it increases HIV prevention knowledge and self-reported risk for HIV
[16]; and when it partially replaces clinician-delivered care in methadone treatment, it also improves opioid abstinence rates
[17].

Seva’s recovery support elements are based on A-CHESS, an evidence-based smartphone program designed to help people in recovery from drug and alcohol addiction prevent relapse. A-CHESS helps patients meet the challenges they often face, such as loneliness and isolation, transportation, managing the treatment regimen, and getting informal support. A-CHESS also addresses issues such as cravings and insufficient coping skills in high-risk situations. A-CHESS is based on research on the principles of effective continuing care for substance use disorders (long duration, assertive outreach, monitoring, prompts, action planning, peer and family support, and case management). The research team that developed A-CHESS has studied and designed similar systems that have been effective for patients suffering from lung cancer, breast cancer, asthma, and HIV
[2,3,18-36]. In a randomized trial of patients discharged from residential addiction treatment, patients with A-CHESS had 57% fewer risky drinking days than patients in the control group
[37].

Although Seva was built from two existing programs, TES and A-CHESS, the Seva user experiences one seamless system with many links between elements. For example, upon completing a skill-building module, the patient may be shown a link to a discussion group where peers are discussing the topic of the module, and provided links to further information on the topic. Similarly, patients whose responses to check-in items indicate a potential problem may see a link to skill-building related to that problem, or be shown personal stories from other patients who have dealt with the same problem. Patient-entered data are also uploaded and presented via a web-based dashboard that FQHC clinicians can use to monitor the status of their Seva users. The dashboard includes items that patients self-report using their mobile devices, such as sleep troubles and relationship problems that may signal an imminent relapse; whether the patient has attended recovery meetings or completed other elements of the treatment plan; and the patient’s relapse risk and protection factors. The dashboard can be customized for each clinic to display indicators that clinicians deem important for clinical decision-making.

### Study focus: implementation

Because Seva has an established evidence base, this research focuses mainly on implementation and organizational impact; some patient-level outcomes are included, but they will be examined in the aggregate. Our goal is to implement a system that has already proven effective in specialty addiction treatment in primary-care settings. The implementation model we are testing (detailed below) is distinguished by several characteristics: an effort to actively prepare the environment for implementation; the use of an organizational coach; the use of rapid-cycle tests; and an early, specific effort to address sustainability. The implementation model is rooted in the field of systems engineering, a multi-disciplinary field that integrates concepts from psychology, economics, social science, and statistics. The implementation model reflects the multi-disciplinary ethic of systems engineering.

We will study organizational change resulting from implementing Seva in 3 FQHCs over a three-year period. We will study elements of our implementation model by using mixed-methods analysis. Our study seeks answers to three broad research questions: how can Seva be implemented in primary care settings efficiently and effectively; to what extent do patients and staff accept and use Seva; and how does Seva affect clinical care for patients and staff?

## Methods/Design

### Implementation model

Our implementation strategy combines three evidence-based organizational change strategies: the Program Planning Model (PPM)
[38,39], the NIATx quality improvement model
[40,41], and core concepts from Rogers’s diffusion of innovations research
[42]. The PPM comes from the literature of organizational behavior; NIATx, from systems engineering; and Rogers, from community-based diffusion. The PPM addresses interpersonal, organizational and environmental variables that promote sustainability. By focusing on socio-political aspects of change in community-based organizations, use of the PPM has led to greater community acceptance than seen in comparison groups
[38,39]. The NIATx model, an extensively evaluated and widely adopted organizational change model in addiction treatment, provides an evidence-based approach to implementation by optimizing processes that create a welcoming environment for change
[40,41]. Rogers’s diffusion of innovations research identified characteristics of innovations associated with successful implementation and sustainability
[42]. Rogers’s research complements the NIATx model by emphasizing ways to adapt an innovation for a specific setting, thus maximizing its adoption potential. Combined, these strategies make up the implementation model shown in Figure 
1.

**Figure 1 F1:**
[figure not shown]
Implementation model.

The model has 4 phases: i) ‘Initiate’ involves bringing together and training key people at each site; ii) ‘Prepare’ ensures that the FQHC environment is welcoming to Seva, the implementation plan adapts to the unique characteristics of the FQHC, and the technology is developed to maximize its chance of success; iii) ‘Improve’ involves conducting a series of rapid-cycle tests of ideas that emerge from earlier phases; and iv) ‘Implement’ involves using, monitoring and sustaining the technology. Organizational coaching will play a key role in helping clinics implement Seva successfully. We recently completed a randomized trial in 201 addiction treatment agencies in which coaching proved to be the most cost-effective approach to quality improvement among several strategies tested
[43]. An implementation coach will work with each FQHC to advise, encourage and monitor progress.

### Settings for implementation

We worked with the National Association of Community Health Centers to identify a set of FQHCs with established electronic health records. We focused on FQHCs with electronic health records because healthcare reform has been pushing FQHCs in this direction, and we believe it will be important to understand how Seva relates to existing clinic technology. From the pool of FQHCs that met these criteria, we selected an FQHC affiliated with the University of Wisconsin as our first implementation site; as a second site, a relatively small, rural, freestanding FQHC with integrated behavioral health services (including addiction treatment); and as a third site, an urban FQHC that serves a largely minority population. In selecting sites, we strove to maximize diversity in both patient populations and organizational structures to better understand how environment affects implementation. We included only three FQHCs in order to conduct an intensive, mixed-methods assessment at each clinic, which we believe will be more informative for the ultimate purpose of dissemination than randomizing a larger sample of organizations and studying implementation at a surface level.

### Timeline

Data will be collected from each FQHC for 48 months using a combination of data sources, including electronic health records, staff surveys/interviews, and patient surveys/interviews. We are collecting staff survey data every 6 months for 36 months, patient survey data every 6 months for 18 months, and aggregated EHR data for 48 months to cover the full time frame from the beginning of the pretest period at FQHC 1 to the end of the posttest period at the FQHC 3. Figure 
2 shows more information about the project timeline. Retrospective data collection will take place during the pretest period, using aggregated patient data from clinics’ electronic health records. During the pretest period, sites will also seek to identify potential patient candidates for recruitment. Full-scale implementation occurs during the subsequent 12 months, during which the sites receive coaching and actively recruit patients to use Seva. The sites will continue to be monitored during a post-test/sustainability period. During this period, sites may continue recruiting patients to use Seva, but without grant funding for phone/internet support or organizational coaching.

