### Study design

Our study uses a non-concurrent multiple-baseline design in which the start of the intervention period is staggered at the three sites by six months. The multiple-baseline design provides the intervention to all participants, but isolates the independent variable by introducing the intervention at specified points. Using the clinic as the unit of analysis, this single-subject approach will closely track the timing of intervention elements and repeatedly measure outcomes at the organizational level, including aggregated effects on clinicians, patients and practices. After pilot testing Seva at the first FQHC and improving Seva and the overall implementation strategy, we will introduce Seva at the second FQHC and then, six months later, at the third FQHC. Each FQHC acts as its own pretest control. During the 48-month data collection period, core organizational indicators will be measured via a staff survey (administered every 6 months) and the clinics’ electronic health records (aggregated across patients). While the non-concurrent multiple-baseline design may not provide as strong a basis for causal inference as a large RCT, we believe it is the appropriate design for evaluating the organizational impact of a system that has already been shown effective in RCTs of patients
[45]. We will also collect a set of standard CHESS/TES measures via a patient survey for comparison to previous studies that tested these technologies in RCTs, and to conduct exploratory analyses. The patient survey also provides supplemental clinical information not routinely collected in the clinics (*e.g*., addiction severity, quality of life, etc.).

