#### Adoption

In assessing adoption at the clinic level, we will report how many FQHCs were approached to participate and how many signed on to implement Seva. We will compare organizational characteristics of participating FQHCs to the more than 1,000 FQHCs in the United States, based on public reports required of these organizations by the federal government. We will gather qualitative data to assess which aspects of organizational structure affect implementation. To assess adoption at the staff level, clinic site coordinators will make a list of all staff members who see potential substance-using patients in primary or behavioral care, and invite these staff to complete surveys six months prior to the implementation period and every six months thereafter. The surveys include questions on job function (*i.e*., physician, behavioral health staff, or RN), which will allow us to assess how representative the respondents are of the clinic staff as a whole, and the Readiness for Implementation Survey
[47], an instrument used to predict the adoption success of information technologies in healthcare. Staff members and patients will take part in qualitative interviews to supplement data provided in the surveys to assess organizational barriers and facilitators related to implementation. We will analyze Seva log files to produce metrics about patterns of system adoption and use by patients and staff and assess the characteristics of individuals who use Seva most and least actively.

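### The fixed 48-month EHR window gives the pilot clinic the shortest pretest (6 to 18 months, the last four of them coached), so its own-control comparison is weaker than it needs to be

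*Protocol article*

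**What the plan says.** The Timeline section states "Data will be collected from each FQHC for 48 months" and describes the EHR component as "aggregated EHR data for 48 months to cover the full time frame from the beginning of the pretest period at FQHC 1" to the close of the posttest at the third clinic. This is one calendar window shared by all three clinics. The same section plans "staff survey data every 6 months for 36 months, patient survey data every 6 months for 18 months" and says of the active phase: "Full-scale implementation occurs during the subsequent 12 months". It gives no length for the pretest or the posttest in the text and refers to Figure 2 for more on the timeline.

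Under Study design, "the start of the intervention period is staggered at the three sites by six months", and "Each FQHC acts as its own pretest control". The abstract lists the periods as "pretest (ending in four months of implementation preparation), active Seva implementation, and maintenance". The section on coaching places a site visit, a walk-through, a workflow assessment, the removal of barriers and then monthly calls inside that four-month preparation.

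The Analysis section specifies a linear model by month with separate level and slope before and after implementation. The implementation indicator only separates time points before implementation from those after it.

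On survey timing, the Adoption section has staff "complete surveys six months prior to the implementation period and every six months thereafter".

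**The concern.** The window is anchored to the pilot's start and the third clinic's end, so the pretest lengths of the three clinics are whatever remains. The pilot, which goes live first, gets the least. Its last four pretest months are also the ones in which the coach is already changing the clinic, yet the model places them in the control segment.

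What is at stake is the pilot's contribution to the EHR outcomes: treatment attendance, healthcare utilization and HIV screening. A short pretest makes its slope, and therefore the slope change, poorly determined. It can also let a seasonal swing pass for a trend or a step. Coached months in the baseline pull the estimated change toward zero if preparation works. With only three clinics, a weak baseline at one of them is a material loss to a design that rests on replication.

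**Working it through.** **1. Length of the pilot's pretest.** Let P1 be the pilot's pretest and S the posttest, in months. Two six-month staggers put go-live at FQHC 3 at 12 months after the pilot. The active phase is 12 months. Then

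P1 + 12 + 12 + S = 48, so P1 = 24 − S.

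FQHC 2 has P1 + 6 pretest months and FQHC 3 has P1 + 12. The 48 months cannot be reproduced uniquely, because neither P1 nor S is given in the text. Two readings fit both the 36-month staff survey and the 48-month window:

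- *Survey months counted per clinic.* They run from −6 to +30 around each go-live. FQHC 3 ends at 12 + 30 = 42 months after the pilot's go-live, so S = 18 and P1 = 48 − 42 = 6.
- *Survey months counted as project time.* They run from −6 to +30 around the pilot's go-live. FQHC 3 ends at 12 + 12 + 6 = 30, so S = 6 and P1 = 48 − 30 = 18. This agrees with the three-year study period in the Background, and with the six-month maintenance follow-up in Table 1 and the Maintenance section.

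S = 12 (P1 = 12) is shown as a midpoint. Subtracting the four preparation months leaves 2, 8 or 14 uncoached months for P1 = 6, 12 or 18.

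**2. Precision.** The model is the one in the Analysis section: intercept, month, implementation, and implementation × month. It is fitted to 48 monthly points with equal weights and independent errors of SD s (assumptions, since the article gives no SD). Time zero is go-live, and each point sits at mid-month. Standard errors are s times the square roots of the diagonal of (X′X)⁻¹.

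| Pretest / post months | SE level | SE slope per month | SE level, preparation months left out |
|---|---|---|---|
| 6 / 42 | 0.88s | 0.239s | 7.1s |
| 12 / 36 | 0.67s | 0.085s | 1.33s |
| 18 / 30 | 0.60s | 0.050s | 0.86s |

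Placing time zero at the first post-implementation point gives level SEs of 0.98s, 0.70s and 0.61s, with the same slope SEs. In that coding, a lag-one autocorrelation of 0.3 raises the level SEs to 1.13s, 0.87s and 0.77s.

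**3. Season.** Fit the same model to a noiseless 12-month cosine of amplitude A with no true effect, and take the worst case over the timing of the peak. The false level change reaches 1.4A, 1.3A and 0.35A for P1 = 6, 12 and 18. The false slope change reaches about 0.40A, 0.14A and 0.018A per month.

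**4. Preparation inside the baseline.** As an illustration, let a lasting effect of 1 build linearly over the four preparation months and then hold. The fitted level change is 0.11, 0.45 or 0.61 for P1 = 6, 12 or 18. Even on the longest reading about 40% of the effect is lost (1 − 0.61 = 0.39).

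**5. After the change.** Starting 24 months before preparation gives 24 + 4 = 28 pretest months. With the same follow-up:

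| Pretest / post months | SE level | SE slope per month | SE level, preparation months left out | Worst seasonal level bias |
|---|---|---|---|---|
| 28 / 42 | 0.49s | 0.027s | 0.60s | 0.29A |
| 28 / 36 | 0.50s | 0.028s | 0.61s | 0.51A |
| 28 / 30 | 0.53s | 0.032s | 0.63s | 0.34A |

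If the preparation months stay in the baseline, the effect in step 4 is estimated as 0.74 in all three rows.

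**The case against.** A reader might infer that the stated timeline leaves the pilot about six pretest months. The documents do not support that as a stated fact. Six months needs an 18-month posttest, which the text nowhere gives. The only maintenance interval it does give is six months, and that leads to 18 pretest months. Figure 2, not available here, may settle the matter. The argument that a patient recruited in month 12 and surveyed for 18 months must fall inside the EHR window does not fix the length either, because the patient survey is a separate data stream.

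A reader might also infer that the pilot cannot serve as its own control. That goes too far. Even with six pretest months, 48 points and four coefficients leave 44 residual degrees of freedom, and both changes can be estimated, though imprecisely. The first site is also a declared pilot, and the plan adds visual comparison within and across clinics.

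At 18 pretest months the loss is moderate. The worst seasonal bias on level is already 0.35A, and the longer extraction leaves it practically unchanged (0.34A).

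Three things stand on every reading. The pilot's pretest is the shortest of the three, by 6 and 12 months. Four of its months are coached but modelled as untreated. And the window's start is a choice, because the data are retrospective and the clinics were selected for having established electronic records.

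**Conclusion.** The concern holds as a design weakness whose size depends on an unstated posttest length. The pilot has 6 to 18 pretest months, 2 to 14 of them uncoached. The level-change SE runs from 0.88s down to 0.60s, and the slope-change SE from 0.239s down to 0.050s per month. Seasonal bias on level can reach 1.4A or 1.3A if the pretest is 6 or 12 months, but only 0.35A at 18. If preparation itself has an effect, the level change is diluted at any of these lengths. The dilution applies at the other two clinics too, but is worst where the baseline is shortest.

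These figures assume independent errors, equal weights and a simple yearly wave. The ramp during preparation is an illustration and not an estimate. The point concerns EHR outcomes only. Substance use, the primary effectiveness outcome, comes from Seva and the patient survey.

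**What to change.** Keep the end of follow-up as planned. Set the start of the retrospective EHR extraction separately for each clinic: at least 24 months before its four-month preparation period, or as far back as its EHR allows. State the resulting pretest months for each clinic, with preparation months counted separately.

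A longer baseline improves precision on every reading (level SE at most 0.53s, slope SE at most 0.032s per month). It reduces the dilution from preparation but does not remove it. It does make it affordable to leave those months out of the control segment, at a level SE of 0.60s to 0.63s instead of up to 7.1s, so the plan should also say how they are handled.

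The cost is a wider date range in an aggregated query that is already planned. The small downside is that older records may be less complete, or absent where a clinic adopted its EHR recently.
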